### **1.6.3. Rationale for parasite genotyping**

The RTS protein is derived from a sporozoite surface antigen of the *P. falciparum* strain NF54. To date, there has been no evidence of parasite-specific immunity. In both the Malaria-005 efficacy study conducted in Gambian men and the Malaria-026 study in Mozambican children, protection was not limited to the NF54 parasite genotype [Bojang 2001; Enosse 2006]. Nevertheless, specimens appropriate for genotyping will be taken on every occasion on which a malaria blood film is taken to enable potential further studies of parasite genetics, should this be deemed necessary.

### **1.6.4. Rationale for study extension**

*Vaccinations began in March 2007. A series of logistic factors, including a change of supplier for the rabies control vaccine leading to interruption in delivery of the study vaccine, and lower than expected recruitment rates resulted in a variable delay of vaccination, such that surveillance post Dose 3 began in May 2007 for some children, but in October 2007 for others. 12 months of surveillance post Dose 3 are planned according per protocol, so children will finish surveillance in the period June 2008-October 2008.*

*The high malaria transmission season is June-October in Kilifi and March-August in Korogwe. In this amendment dated April 2008, we propose to continue active and passive case detection in all children until the end of the transmission season. This will result in a variable length of follow up, but all children will end surveillance on the same date in each site (October 2008 in Kilifi, September 2008 in Korogwe). Surveillance is therefore extended through the transmission season for all subjects and is likely to produce an increase in power.*

*There will be two additional visits. The first visit (Clinic Visit 8) at the start will be to request informed consent. The second visit (Clinic Visit 9) at the close of study will allow to assess safety at the final time-point, and to obtain a cross-sectional bleed in order to study parasite prevalence at the end of the malaria transmission season. The duration of protection may be linked to the duration of immunogenicity, and so serum will be used from this final time-point to measure vaccine-induced antibodies to the circumsporozoite antigen (CS).*

*Amended 17 April 2008*

## 2. OBJECTIVES

### 2.1. Primary objective

**NOTE:** *In the event that malaria rates are lower in the year of the study the cross sectional survey, unblinding and analysis scheduled at 4½ months post Dose 3 will be delayed until approximately 245 children have experienced an episode.*

- For RTS,S/AS01E when administered as 3 doses intramuscularly on a 0, 1, 2-month schedule to children aged 5 to 17 months living in malaria-endemic areas:
  - to assess efficacy against clinical malaria disease meeting the primary case definition (detected on active and passive case detection) with *P. falciparum* over a period of 4½ months (starting two weeks post Dose 3).

Refer to Section 10.1 for definition of the primary endpoint.

### 2.2. Secondary objectives

**NOTE:** *In the event that malaria rates are lower in the year of the study the cross sectional survey, unblinding and analysis scheduled at 4½ months post Dose 3 will be delayed until approximately 245 children have experienced an episode.*

- For RTS,S/AS01E when administered as three doses intramuscularly on a 0, 1, 2-month schedule to children aged 5 to 17 months living in malaria-endemic areas:
  - to assess efficacy against clinical malaria disease meeting the secondary case definition (detected on active and passive case detection) with *P. falciparum* over a period of 4½ months (starting two weeks post Dose 3).
  - to assess safety and reactogenicity until 4½ months post Dose 3.
  - to assess the antibody responses to the hepatitis B surface (HBs) antigen up to 1 month post Dose 3.
  - to assess the antibody responses to the circumsporozoite (CS) antigen up to 4½ months post Dose 3.
  - to assess the T-cell immune response to CS antigen up to 1 month post Dose 3 in an Intracellular Cytokine Assay.
  - to assess the effect on hemoglobin, parasite prevalence and parasite density

Refer to Section 10.2 for definitions of secondary endpoints.

### 2.3. Tertiary objectives

- For RTS,S/AS01E when administered as three doses intramuscularly on a 0, 1, 2-month schedule to children aged 5 to 17 months living in malaria-endemic areas:
  - to assess efficacy against clinical malaria disease (detected on active and passive case detection) with *P. falciparum* over a period of 12 months post

Dose 3.

- to assess safety between 4½ months post Dose 3 and 12 months post Dose 3.
- *To assess safety until October 2008 in Kilifi and September 2008 in Korogwe.*

*Amended 17 April 2008*

- *To assess efficacy against clinical malaria (detected on active and passive case detection) with P. falciparum from Dose 3 until October 2008 in Kilifi and September 2008 in Korogwe.*

*Amended 17 April 2008*

- to assess antibody responses to the circumsporozoite (CS) antigen at 12 months post Dose 3.
- to assess antibody responses to the hepatitis B surface (HBs) antigen at 12 months post Dose 3.
- *to assess antibody responses to the circumsporozoite (CS) antigen at a cross-sectional survey occurring in October 2008 in Kilifi and September 2008 in Korogwe.*

*Amended 17 April 2008*

- to assess the T-cell immune response to CS antigen up to 12 months post Dose 3 in an Intracellular Cytokine Assay.

Refer to Section 10.3 for definitions of tertiary endpoints.

## 2.4. Exploratory objectives

- For RTS,S/AS01E when administered as three doses intramuscularly on a 0, 1, 2-month schedule to children aged 5 to 17 months living in malaria-endemic areas:
  - to evaluate the cellular immune responses to CS antigen up to 12 months post Dose 3 using cytokine elispot assay
  - to evaluate the regulatory T-cell immune response to CS and blood stage malaria antigens at 4½ months post Dose 3.
  - to evaluate the humoral immune response to malaria blood stage antigens up to 12 months post Dose 3

Refer to Section 10.4 for definition of tertiary endpoint.

### 3. STUDY DESIGN OVERVIEW

[figure not shown]

**KEY:** BS; Blood Sample. Vacc; Vaccination. ACD; Active Case Detection. *Extension; extension of the single-blind phase*  
Clinic Visit 7 and Clinic Visit 8 can take place on the same day. For subjects who do not present at Clinic Visit 7, an interval of 14 to 17 months post Clinic Visit 2 to Clinic Visit 8 is acceptable.

† Month 14-19 at Clinic Visit 9 corresponds to October 2008 in Kilifi and September 2008 in Korogwe

\*In the event that malaria rates are lower in the year of the study, the cross sectional survey, unblinding and analysis will be delayed until sufficient cases have accumulated to have an adequately powered analysis.

*Amended 17 April 2008*

- Experimental design: Phase IIb, two-center, double blind (observer blind, participant blind), randomized (1:1 ratio), controlled trial with two groups.
- Healthy male and female children aged 5 to 17 months will be screened; those determined to be eligible, based on the inclusion and exclusion criteria, will be enrolled in the study.
- Hepatitis B immunization status will be recorded on the CRF at study entry.
- All EPI vaccines given throughout the trial will be recorded in the CRF.
- Route of administration: all vaccines will be administered by the intramuscular route to the left deltoid.
- Each child will be observed for at least 60 minutes after vaccination to evaluate and treat any acute adverse events (AEs).
- There will be a 7-day follow-up period for solicited AEs post-vaccination: Day 0 evaluation will be carried out by the study physician at the study center. Subsequently, trained field workers will visit the children to solicit adverse events (AEs) on days 1 to 6 after each vaccination.
- There will be a 30-day (day of vaccination and 29 subsequent days) follow-up after each vaccine dose for reporting unsolicited symptoms.
- Serious adverse events (SAEs) will be recorded throughout the study period. Prior to vaccination, any SAEs due directly to study procedures will be captured. All SAEs will be captured beginning with the administration of the first dose and ending 12 months after Dose 3 of study vaccines.

- All children will be followed by Active Case Detection (ACD) and Passive Case Detection (PCD) for a period extending to one year post Dose 3, *and then, under a separate consent, until October 2008 in Kilifi and September 2008 in Korogwe.*  
*Amended 17 April 2008*
- Two cross sectional surveys for efficacy will be performed at 4½ and 12 months post Dose 3 to determine parasite prevalence, parasite density and hemoglobin, *and under a separate consent, a third cross-sectional survey for efficacy will be performed in October 2008 in Kilifi and September 2008 in Korogwe to determine parasite prevalence, parasite density and hemoglobin.*  
*Amended 17 April 2008*
- In the event that malaria rates are lower in the year of the study the cross sectional survey, unblinding and analysis scheduled at 4½ months post Dose 3 will be delayed until approximately 245 children have experienced an episode.
- Anti-CS antibody titers will be determined at baseline, 1, 4½ and 12 month post Dose 3 *and under a separate consent, at a cross-sectional survey occurring in October 2008 in Kilifi and September 2008 in Korogwe* in all study participants.  
*Amended 17 April 2008*
- Anti-HBs antibody titers will be determined at baseline, 1 and 12 months post Dose 3 in all study participants.
- CS-specific IFN-γ ELISPOT responses will be evaluated at baseline, 1 and 12 months post Dose 3 in study participants at KEMRI, Kenya.
- Regulatory T-cell immune response will be determined at 4½ months post Dose 3 in all study participants.
- Anti-malaria blood stage humoral immunity will be determined at baseline, 1 and 12 months post Dose 3 in all study participants.
- Timing of final analysis is projected for 4½ months post Dose 3. The study will continue in a single-blind manner and be reported as an annex at the end of the study.
- The final analysis is projected to occur after the completion of 4 months of surveillance, at which time it is assumed that 36% of children in the control group will have been affected by a malaria episode. Assuming a true vaccine efficacy of 30%, 400 evaluable subjects per group will have 90% power to detect a difference between the groups using a two sided Fischer exact test with alpha level of 5%.
- The vaccine research teams will ensure that insecticide treated bed net use is optimized in the study population.
- Data collection: conventional Case Report Form (CRF).

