|                                      |                                                                                                                                                                                                                                                                                                                                                                                                                                                                                                                                                                                                                                                                                                                |
|--------------------------------------|----------------------------------------------------------------------------------------------------------------------------------------------------------------------------------------------------------------------------------------------------------------------------------------------------------------------------------------------------------------------------------------------------------------------------------------------------------------------------------------------------------------------------------------------------------------------------------------------------------------------------------------------------------------------------------------------------------------|
| Blinding:                            | A procedure in which one or more parties to the trial are kept unaware of the treatment assignment in order to reduce the risk of biased study outcomes. In a single-blind trial, the investigator and/or his staff are aware of the treatment assignment but the subject is not. In an observer-blind study, the subject and the study personnel involved in the clinical evaluation of the subjects are blinded while other study personnel may be aware of the treatment allocation. When the investigator and sponsor staff who are involved in the treatment or clinical evaluation of the subjects and review/analysis of data are also unaware of the treatment assignments, the study is double blind. |

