## **5.9. Active case detection (ACD) of Malaria**

Active Case Detection of malaria will commence two weeks post Dose 3.

At each visit the axillary temperature of each subject will be taken and if  $\geq 37.5^{\circ}\text{C}$  a blood slide and a rapid test (OptiMal®, Flow Incorporated, Oregon, USA) to determine malaria parasitemia will be taken.

If the child is documented to be febrile and the rapid test is positive, the field worker will give the child antimalarial chemotherapy and inform a study clinician. Mobile phones will be provided to study staff. Appropriate to the clinical features of the illness, transfer of children will be arranged to a health facility, if necessary. Amended 23 October 2006.

If the child is documented to be febrile and the rapid test is negative, antimalarial chemotherapy will not be administered by the field worker. A study physician will be informed. Appropriate to the clinical features of the illness, the child's parent(s)/guardian(s) will be advised to attend their nearest health facility to be reviewed by clinically qualified personnel (medical or nursing) or transfer will be arranged to the secondary care facility.

If the parents/guardians report the child has had a fever but the axillary temperature is  $< 37.5^{\circ}\text{C}$ , the field worker will revisit the child between 6 to 12 hours later to recheck the temperature and if the temperature is measured as  $\geq 37.5^{\circ}\text{C}$  a blood slide and rapid malaria test will be taken. If the test is positive, the child's case will be managed as above.

If no fever is documented at the revisit, a study physician will be informed. Appropriate to the clinical features of the illness, the child's parent(s)/guardian(s) may be advised to attend their nearest health facility to be reviewed by clinically qualified personnel (medical or nursing), or transfer will be arranged to the secondary care facility or on a study physician's advice, no further action is required. The parent(s)/guardian(s) will be informed that if they have concerns, they may always attend their nearest health facility to have their child reviewed by clinically qualified personnel.

Treatment will be indicated by rapid test result. Blood slides for parasitemia will not be read in real time to guide case management routinely. Blood slides will always be taken in duplicate.

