## **6.5. Method of blinding and breaking the study blind**

Data pertaining to RTS,S/AS01E or rabies vaccine will be collected in a double blinded (observer blinded) manner. 'Double blinded (observer blinded)' means that the vaccine recipient and their parent(s)/guardian(s) as well as those responsible for the evaluation of safety and immunogenicity endpoints will all be unaware which treatment, RTS,S/AS01E or rabies vaccine, was administered to a particular subject. The only study staff aware of the vaccine assignment for RTS,S/AS01E or rabies vaccine will be those responsible for the storage and preparation of vaccines; these staff will play no other role in the study.

Code break envelopes, for each study enrolled subject and associating each treatment number with a specific vaccine, will be kept by the Local Safety Monitors in Kenya and Tanzania as well as by Central Safety at GSK Biologicals, Rixensart in a safe and locked place with no access for unauthorized personnel.

If deemed necessary for reasons such as safety or to guide treatment in a subject exposed to rabies, the relevant Local Safety Monitor together with the GSK Biologicals Central Safety Contact will unblind the specific enrolled subject.

A formal reporting and analysis plan (RAP) will be developed. Once the study is completed and the GSK Biologicals reference database locked, GSK Biologicals will be responsible for initiating the execution of the statistical analysis plan in collaboration with KEMRI, JMP and MVI and breaking the blind.

GSK Biologicals' policy (incorporating ICH E2A guidance, EU Clinical Trial Directive and Federal Regulations) is to unblind any serious adverse event (SAE) report associated with the use of the investigational product, which is unexpected and attributable/suspected, prior to regulatory reporting. The Clinical Safety Physician is responsible for unblinding the treatment assignment in accordance with specified time frames for expedited reporting of SAEs (Refer to Section 8.8).

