### **10.3. Tertiary endpoints**

#### **Efficacy**

- Time to first case of malaria meeting the primary case definition over a period starting 14 days after Dose 3 and extending for 12 months *and a period starting 14 days after Dose 3 and extending until October 2008 in Kilifi and September 2008 in Korogwe.*

*Amended 17 April 2008*

- Time to first case of malaria meeting the secondary case definition over a period starting 14 days after Dose 3 and extending for 12 months *and a period starting 14 days after Dose 3 and extending until October 2008 in Kilifi and September 2008 in Korogwe.*

*Amended 17 April 2008*

- Multiple events of malaria meeting the primary case definition over a period starting 14 days after Dose 3 and extending for 12 months *and a period starting 14 days after Dose 3 and extending until October 2008 in Kilifi and September 2008 in Korogwe.*

*Amended 17 April 2008*

- Multiple events of malaria meeting the secondary case definition over a period starting 14 days after Dose 3 and extending for 12 months *and a period starting 14 days after Dose 3 and extending until October 2008 in Kilifi and September 2008 in Korogwe.*

*Amended 17 April 2008*

- Parasite prevalence and density at 12 months post Dose 3 *and in October 2008 in Kilifi and in September 2008 in Korogwe.*

*Amended 17 April 2008*

- Hemoglobin at 12 months post Dose 3 *and in October 2008 in Kilifi and in September 2008 in Korogwe.*

*Amended 17 April 2008*

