## **10.10. Final analyses**

The final analysis will be conducted on data collected until Clinic Visit 6. The study will continue in a single-blind manner. This additional information will be appended to the study report.

In the event that malaria rates are lower in the year of the study the unblinding and analysis following Clinic Visit 6 will be delayed until approximately 245 children have experienced an episode. This analysis will have 90% power assuming true vaccine efficacy to be 30%.

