#### **10.10.4. Analysis of safety**

##### **10.10.4.1. Secondary safety endpoints**

Safety will be analyzed on the Total Vaccinated Cohort. If the percent of enrolled subjects excluded from the ATP cohort for analysis of safety is more than 5%, a second analysis based on this ATP cohort will be performed to complement the Total Vaccinated Cohort analysis.

Analysis of the occurrence of SAEs will be performed on the Total Vaccinated Cohort. The proportion of subjects with an SAE, classified by the MedDRA preferred term level, reported from study start until Clinic Visit 6 (end of the double-blind phase) will be tabulated with exact 95% CI.

The proportion of subjects reporting an AE (unsolicited) 30 days post each vaccination, classified by the MedDRA preferred term level, reported from study start until the end of the double-blind phase will be tabulated with exact 95% CI.

The percentage of subjects with at least one local adverse event (solicited and unsolicited), with at least one general adverse event (solicited and unsolicited) and with any adverse event during the solicited follow-up period will be tabulated with exact 95% CI after each vaccine dose and overall. The percentage of doses followed by at least one local adverse event (solicited and unsolicited), by at least one general adverse event (solicited and unsolicited) and by any adverse event will be tabulated, overall vaccination course, with exact 95% CI. Similar tables will be generated for Grade 3 events, the relationship of the event to vaccination.

The percentage of subjects reporting each individual solicited local and general adverse event during the solicited follow-up period will be tabulated with exact 95% CI. The percentage of doses followed by each individual solicited local and general adverse event will be tabulated, overall vaccination course, with exact 95% CI. Similar tables will be generated for Grade 3 events, the relationship of the event to vaccination and for fever and temperature in 0.5°C increments.

Biochemistry (ALT and creatinine) and hematology (hemoglobin, WBC, platelets) values that are outside of the reference ranges will be described for Clinic Visit 6 (end of double-blind phase). Frequency distribution of results by toxicity grades will be tabulated by group.

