### Determination of parasitemia

Slides for the determination of parasitemia will be made and read in duplicate. Estimates of asexual *P. falciparum* parasite density will be made at the investigator's sites according to laboratory SOPs.

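### After the Visit 6 analysis the protocol allows site staff to know the arm, against Section 6.5, so the later part of the 12-month and extension malaria follow-up is open to biased case detection

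*Protocol*

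**What the plan says.** Section 3 projects the final analysis for 4½ months post Dose 3 and then states: "The study will continue in a single-blind manner and be reported as an annex at the end of the study". Section 10.10 sets the change of phase: "The final analysis will be conducted on data collected until Clinic Visit 6. The study will continue in a single-blind manner". Section 10.10.4.1 confirms where the double-blind phase stops, describing SAEs as "reported from study start until Clinic Visit 6 (end of the double-blind phase". Table 3 heads the later columns as single-blind, and the Section 3 key calls the 2008 extension an extension of that phase. Note B to Table 3 adds that the later weekly visits stay in the double-blind phase if the Visit 6 survey is postponed.

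The Glossary gives the term its meaning: "In a single-blind trial, the investigator and/or his staff are aware of the treatment assignment but the subject is not".

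Section 6.5 describes a different arrangement. Only staff who store and prepare vaccine know the assignment, and they have no other role. The sponsor breaks the blind "Once the study is completed and the GSK Biologicals reference database locked". Section 6.5 names the evaluators of safety and immunogenicity as blinded. It does not name those who detect malaria cases.

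The tertiary clinical-malaria endpoints in Section 10.3 run "over a period starting 14 days after Dose 3 and extending for 12 months" and, in a second version, to October 2008 in Kilifi and September 2008 in Korogwe.

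**The concern.** Who is blinded, and until when, is a design rule, and the protocol states it in two incompatible ways. Under the single-blind label, field workers, clinicians and slide readers may know the arm. No passage says that they stay blinded after Visit 6. Section 6.5 also has the analysis carried out in collaboration with KEMRI and JMP, the two teams that run the sites, and does not separate that role from their field role.

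Staff actions help decide what becomes a case. In active detection (Section 5.9) a field worker takes the temperature that determines whether a slide is made. When a parent reports fever but none is measured, "the field worker will revisit the child between 6 to 12 hours later to recheck the temperature". If there is still no fever, onward referral depends on a study physician's advice, and referral brings a further temperature measurement under the passive-detection procedures. The primary case definition then needs more than 2 500 parasites per µL, and estimates of "parasite density will be made at the investigator's sites according to laboratory SOPs".

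At stake are the later VE estimates, which bear on duration of protection, and investigator-judged SAE causality after Visit 6.

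**Working it through.** **1. The passages side by side.**

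| Question | Sections 3 and 10.10, with the Glossary | Section 6.5 |
|---|---|---|
| Who may know the arm after Visit 6? | The investigator and/or staff | Storage and preparation staff only |
| When is the blind broken? | For the analysis at about 4½ months post Dose 3, with surveillance continuing | Once the study is completed and the database locked |

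Both cannot hold for the period after Visit 6.

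**2. The plan's own figure.** Section 10.6.1 gives 400 × 0.36 + 400 × 0.252 = 144 + 100.8 = 244.8, stated as 245. Exact power of the two-sided Fisher test for 36% against 25.2% with 400 per group is 0.902, against the stated 90%. Both reproduce. They concern the double-blind primary analysis; the present point does not rest on them.

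**3. How much follow-up is exposed.** The windows open 14 days after Dose 3 (about Month 2½). Visit 6 is at Month 6½, so the first 4 months are double-blind if Visit 6 is on time.

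- 12-month window: (12 − 4)/12 = 67% after Visit 6. Counted to Visit 7 at Month 14, it is 7.5/11.5 = 65%.
- Extension, Visit 9 at Month 14 to 19: length 11.5 to 16.5 months, so 7.5/11.5 = 65% to 12.5/16.5 = 76%.
- Primary and secondary efficacy endpoints: the malaria windows last 4 months and the survey measures are taken at Visit 6, so none falls after it.

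**4. Illustration of the effect.** Let s be the share of cases after Visit 6 and r the detection of cases in vaccinees relative to controls in that period. Then

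observed VE = 1 − (1 − true VE) × [(1 − s) + s × r].

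The documents give neither s nor r; both are assumptions. Taking s = 0.67 from the share of time:

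- r = 0.95: the bracket is 0.33 + 0.67 × 0.95 = 0.9665. True VE 30% gives 1 − 0.7 × 0.9665 = 32.3%; true VE 0 gives 3.4%.
- r = 0.90: the bracket is 0.33 + 0.67 × 0.90 = 0.933. True VE 30% gives 1 − 0.7 × 0.933 = 34.7%; true VE 0 gives 6.7%.

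If postponement or seasonality lowered s to 0.5, the same r values give 31.8% and 33.5% for true VE 30%, and 2.5% and 5% for true VE 0. The formula is a simple rate-ratio calculation. For time to first episode, a child whose first case precedes Visit 6 cannot be affected, so s there is the share of first cases.

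**The case against.** The strongest reply is that a Glossary entry is not an access rule. No passage releases individual codes to the sites. Section 6.5 leaves the code envelopes with the Local Safety Monitors and the sponsor's Central Safety. The Glossary also reserves double-blind for trials in which the sponsor's analysts are unaware too, so the Visit 6 analysis alone would end that status without any field worker learning an allocation. This stands in part: staff knowledge is permitted, not established. It does not remove the conflict, because the Glossary has a term, observer-blind, for the case in which clinical evaluators stay unaware, and the protocol does not use it for this phase.

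The procedures also limit the risk. Active visits are weekly for every child, the temperature threshold is measured, the revisit is mandatory and prompted by parents who remain blinded, and slides are read in duplicate. Only slides that complete the SOP reading process count (Section 10.9.4), and those SOPs, which may mask readers, are not at hand. These safeguards reduce the risk without removing it, since measurement, referral after an afebrile revisit and slide reading still rest with staff.

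Three stronger readings are tempting, and the documents do not support them:

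- A reader might infer that the 12-month and extension endpoints are collected wholly in the single-blind phase. Their windows open in the double-blind phase.
- A reader might infer that every tertiary efficacy endpoint is exposed. Hemoglobin is a laboratory value. Survey slides are taken whatever the symptoms (with an exception at Visit 9 for afebrile children seen within 14 days of Visit 7), so selective detection does not arise there.
- A reader might apply the assumed 5-10% deficit to every case and obtain 33.5-37% from a true VE of 30%. Cases before Visit 6 are found under double-blind conditions and cannot carry it.

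**Conclusion.** The conflict is real and should be resolved. As written, site staff may know the arm during the part of the tertiary clinical-malaria windows that follows Visit 6, about 8 of 12 months if Visit 6 is on time, and during SAE causality assessment in that period. The size of any bias is unknown. On assumed figures (5-10% under-detection in vaccinees, two thirds of cases after Visit 6), a true VE of 30% reads as about 32-35% and a true VE of 0 as about 3-7%. The primary and secondary efficacy conclusions do not depend on this. A reader might go on to infer that staff did know the arm, or that detection did differ by arm; the protocol is evidence of neither. It is a worthwhile, inexpensive improvement and does not threaten the main result.

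**What to change.** State in Sections 3, 6.5 and 10.10 that, after the Visit 6 analysis:

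- individual allocation is known only to the sponsor's analysis group, vaccine preparation staff and the emergency code-holders already named;
- investigators, study clinicians, field workers, slide readers and SAE assessors stay blinded to individual allocation until Clinic Visit 9 data are locked;
- Visit 6 results go to the sites by group only.

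Amend the Section 6.5 sentence on breaking the blind so that it allows for the Visit 6 analysis, add malaria case detectors to those it names as blinded, and align the Glossary or the phase label with the rule. The existing emergency unblinding route need not change.

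The cost is protocol wording and control of access to the code. The drawback is that sites wait for individual codes until the extension closes.
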